## Abstract

**Background:**

Osteoarthritis (OA) is a chronic and painful condition where the articular cartilage surfaces progressively degenerate, resulting in loss of function and progressive disability. Obesity is a primary risk factor for the development and progression of knee OA, defined as the “metabolic OA” phenotype. Metabolic OA is associated with increased fat deposits that release inflammatory cytokines/adipokines, thereby resulting in systemic inflammation which can contribute to cartilage degeneration. There is currently no cure for OA. Prebiotics are a type of dietary fiber that can positively influence gut microbiota thereby reducing systemic inflammation and offering protection of joint integrity in rodents. However, no human clinical trials have tested the effects of prebiotics in adults with obesity suffering from knee OA. Therefore, the purpose of this double-blind, placebo-controlled, randomized trial is to determine if prebiotic supplementation can, through positive changes in the gut microbiota, improve knee function and physical performance in adults with obesity and knee OA.

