### Design, participants, and setting

The study is a single-center (all testing and visits occurring at the Human Performance Laboratory, University of Calgary, Calgary, Alberta, Canada), double blind, placebo-controlled randomized trial in which 60 adults (age 30–75 years) with obesity (body mass index (BMI) > 30 kg/m^2^) will be randomly assigned for six (6) months to either a placebo (*n* = 30; 6.6 g/day maltodextrin) or prebiotic (*n* = 30; 16 g/day oligofructose-enriched inulin) group. The prebiotic dosage selected for the present study is based on the dosage commonly used in previous studies with inulin and/or oligofructose that targeted metabolic outcomes including weight loss, adiposity, glycemia, and inflammatory markers [24–26, 30–33]. The age range was selected based on the increasing incidence rates for knee osteoarthritis that occur from the approximate age of 30 upwards [34]. We limited the upper end of the age range to 75 years given the known shift in gut microbiota composition that occurs with aging [35] that could potentially confound the study outcomes. Participants will visit the Human Performance Laboratory at baseline, 3, 6, and 9 months. At each visit, data will be collected for anthropometrics, knee function, knee pain, stool and blood samples, and questionnaires to monitor daily activities, food intake, and quality of life.

Participants will be recruited from the Alberta Hip and Knee Clinic and Rocky Mountain Health Clinic both located in Calgary, Alberta, Canada. Additionally, recruitment posters will be displayed on public notice boards and social media venues will be used to highlight the objectives of the study so that potential participants from the community in Calgary and surrounding area can contact the research team for more information. Potential participants will be screened for concomitant knee osteoarthritis and BMI > 30 kg/m^2^ and assessed for eligibility as per inclusion and exclusion criteria listed below.

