### Gut microbiota and inflammation related outcomes

Participants will be instructed on proper methods for stool sample collection and all materials provided in a convenient stool collection kit. Participants will collect 2 tablespoons of stool every 3 months. The container will be sealed, placed in a biohazard bag, transported to the lab, and stored at − 80 °C until processed.

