### Analysis

Statistical analysis will be performed using SPSS 26.0 software (IBM, New York, USA). Results will be considered statistically significant if *p* ≤ 0.05. Baseline descriptive data between the prebiotic and placebo groups will be compared using chi-square for categorical variables and t tests for continuous variables. The primary analysis will be on an intent-to-treat basis, with a secondary analysis performed on a per-protocol basis with all subjects that complete the intervention. The primary outcome measurement of performance-based tests will be expressed as mean with standard deviation and analyzed using a two-way mixed model ANOVA (2 × 4) with a within-subject factor (time) of 4 levels (0, 3, 6, and 9 month time points) and one between factor (group) of 2 levels (prebiotic and placebo). A similar statistical approach will be used to test differences in the secondary outcome measurements including DXA body scans, blood tests, stool collection, and questionnaires. For the microbiota analysis, Phyloseq R package will be used for downstream analysis. Alpha diversity will be measured by calculating the Shannon and Simpson index. Beta diversity will be evaluated using non-metric multidimensional scaling (NMDS) on Bray-Curtis dissimilarity matrix. Differential abundance analysis between groups will be carried out using LEfSe conda package. To account for multiple comparisons, a false discovery rate (FDR) correction will be applied and significance set at *p* ≤ 0.05.

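### For gut taxa and community composition, the named methods (LEfSe, NMDS) do not test change from baseline or group by time, although stool is collected at four visits

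*Protocol article*

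**What the plan says.** All of this is in the protocol article.

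- **Sampling.** Under Gut microbiota and inflammation related outcomes: "Participants will collect 2 tablespoons of stool every 3 months". Under Design, participants, and setting: "Participants will visit the Human Performance Laboratory at baseline, 3, 6, and 9 months". Each participant can therefore give four stool samples, the first before treatment.
- **Objective.** The secondary objectives seek a mechanistic understanding by looking at how the gut microbiota and serum markers change in the two arms.
- **Taxa.** Analysis section: "Differential abundance analysis between groups will be carried out using LEfSe conda package". An FDR correction follows. The section does not say which visit is compared or how the baseline sample enters.
- **Community composition.** "Beta diversity will be evaluated using non-metric multidimensional scaling (NMDS) on Bray-Curtis dissimilarity matrix". No test is named beside it.
- **Scalar stool outcomes.** "Alpha diversity will be measured by calculating the Shannon and Simpson index". The primary outcome gets a "two-way mixed model ANOVA (2 × 4) with a within-subject factor (time) of 4 levels (0, 3, 6, and 9 month time points") and a between factor for group, and a similar approach is to be used for "the secondary outcome measurements including DXA body scans, blood tests, stool collection, and questionnaires".
- **Purpose.** The abstract asks whether the prebiotic can "through positive changes in the gut microbiota, improve knee function and physical performance in adults with obesity and knee OA".

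**The concern.** The objective is about change, and the design pays for a baseline sample and three follow-up samples per person. The two methods named for taxa and composition make little use of this. LEfSe rests on a rank comparison between classes of samples treated as independent. It has no participant term, no baseline covariate and no group-by-time term. NMDS draws samples in a low-dimensional plot and gives no p-value or interval for a difference between arms.

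Two things are at stake. If LEfSe is run at one visit, between-person variation that the baseline sample could remove stays in the comparison, and with 30 per arm that may hide real shifts in taxa. If all visits went into one LEfSe run, correlated samples from the same person would count as independent, and the p-values passed to the FDR step would be too small. For composition, an apparent separation on the plot would have no stated inference behind it.

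**Working it through.** The article gives no figure for the microbiota analysis, so there is none to reproduce. The check sizes the two ways in which LEfSe could be run.

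**Inputs**
- 30 participants per arm, 1:1 (Sample size; Randomization).
- 4 samples per person, at months 0, 3, 6 and 9.
- Significance level 0.05 (Analysis), taken as two-sided.
- Correlation ρ of one taxon between visits within a person: not given. Assumed range 0.3 to 0.7, equal for all pairs of visits.

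**Run at one visit.** With equal variance σ² at baseline and follow-up, adjusting for baseline reduces the residual variance to σ²(1−ρ²). The unadjusted comparison therefore carries 1/(1−ρ²) times the variance. Equivalently, 30 per arm unadjusted are worth 30 × (1−ρ²) per arm adjusted.

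**Pooled over four visits.** The design effect is 1 + (4−1)ρ. The true type I error of a nominal 0.05 test is about 2 × [1 − Φ(1.96/√(1+3ρ))]. As a check, a two-group Kruskal-Wallis test was simulated on 3,000 null trials per setting, once on 120 v 120 pooled samples and once on 30 v 30 samples from one visit.

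| ρ | 1/(1−ρ²) | 30 × (1−ρ²) | 1+3ρ | Pooled, formula | Pooled, simulated | One visit, simulated |
|---|---|---|---|---|---|---|
| 0.3 | 1/0.91 = 1.10 | 27.3 | 1.9 | 0.155 | 0.138 | 0.044 |
| 0.5 | 1/0.75 = 1.33 | 22.5 | 2.5 | 0.215 | 0.220 | 0.048 |
| 0.7 | 1/0.51 = 1.96 | 15.3 | 3.1 | 0.266 | 0.255 | 0.045 |

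The one-visit test holds its level, so its weakness is efficiency. The pooled test does not hold its level.

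**Covariate or change score.** With a true shift of 0.7 SD at months 3 and 6, simulated power at month 6 was 0.75, 0.75 and 0.73 for the one-visit rank test at ρ = 0.3, 0.5 and 0.7. For a rank test on simple change from baseline it was 0.60, 0.74 and 0.91. A raw change score can therefore lose power when ρ is low, which is why the fix enters baseline as a covariate.

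The simulations use normal data. For sparse taxa with many zeros the figures are only a guide.

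**The case against.** The strongest reply is that the plan contains no demonstrated error. A reader might infer three stronger faults, and the article supports none of them.

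- **That the whole microbiota analysis ignores the repeated samples.** The same section extends the 2 × 4 mixed ANOVA to stool outcomes. Shannon, Simpson and fecal short-chain fatty acids give one value per sample and fit that model, including its group-by-time term. This part of the objection stands and limits the point to taxa and composition. It does not cover those two, because the microbiota sentences that follow assign them their own methods. If the ANOVA was also meant for taxa, the section names two tests for one outcome without saying which governs.
- **That the plan has a 14–25% false-positive rate.** That rate needs pooled visits, an assumed correlation, and p-values before FDR correction. The article never says that visits are pooled. The ordinary reading, one visit between randomised arms, is valid. This stands too, so the figure is a warning about one way of running LEfSe and not the plan's error rate.
- **That the question of an effect through the microbiota cannot be answered, because nothing links microbiota to function.** Stool and performance are measured at the same visits, so such an analysis remains possible. A condensed article may leave it to the full protocol or the analysis plan. An observational association adjusted for arm would not prove that pathway either.

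It can also be said that baseline adjustment is only a matter of efficiency, that the gain is small at ρ = 0.3 (a ratio of 1.10), and that these outcomes are mechanistic and not primary. That is fair and keeps the point modest. It does not remove it: the article fixes these methods by name, and they do not test the change that the objective asks about.

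**Conclusion.** The point holds for taxon abundance and community composition only. As named, LEfSe does not test change from baseline or group by time, and NMDS tests nothing. The likely cost is lost precision: a single-visit comparison carries 1.10 to 1.96 times the variance of a baseline-adjusted one for ρ from 0.3 to 0.7. That is like having about 27 down to 15 per arm in place of 30. Inflated type I error of about 14–25% per taxon before FDR applies only if the four visits were pooled, which the text leaves open. All these sizes rest on the assumed correlation and on approximately normal data.

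The wording of the purpose needs care for a related reason. Parallel comparisons between arms can show that the microbiota and function each differ. They cannot show that one caused the other.

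**What to change.** 1. Make the inferential taxon analysis a linear mixed model per taxon on centred-log-ratio abundances at months 3, 6 and 9. Include group, visit, group by visit and a participant random effect. Month 0 enters as a covariate and not as an outcome. Apply the FDR correction over taxa to the month-6 group contrast.
2. Test beta diversity by PERMANOVA on month-6 Bray-Curtis distances. Each person then contributes one sample, so the permutations need no restriction. This is a valid comparison of randomised arms, though it does not itself use the baseline sample.
3. Keep LEfSe and NMDS as descriptive displays, and state that LEfSe will not pool visits.
4. Report taxon results as a between-group difference in change, and composition results as a between-group difference at month 6. Do not present either as proof that function improved through the microbiota.

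No new data are needed. The cost is a little more work in R, which is already planned for the microbiota, and less direct comparability with earlier LEfSe results.

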## Discussion

The increased prevalence of adults with co-morbid obesity and knee OA has resulted in a growing demand for aggressive treatment strategies, such as bariatric surgery for substantial weight loss and/or knee joint replacement for pain management at increasingly younger ages. Despite a variety of factors that can play a substantial role in the development and further progression of OA, there is abundant evidence in the literature linking obesity with gut dysbiosis and increased low-level systemic inflammation, thereby contributing to early knee joint degeneration [6–10]. Currently, there is no curative treatment for OA, and patients have difficulties adhering to exercise treatment to improve knee joint function and reduce body weight due to discomfort and pain.

Since obesity is a known modifiable risk factor and there are few effective obesity treatments, a prebiotic diet intervention may offer a solution to improve quality of life in adults with obesity suffering from knee OA by reducing knee joint pain and improving physical function [28, 29]. Through positive changes in the gut microbiota, prebiotics have been shown to reduce low-level systemic inflammation and protect knee joint cartilage in rodent models of obesity [28, 29]. Based on the protective effects of prebiotics on joint health in rats and mice, and the reduction in inflammation in human studies, we hypothesize that prebiotic supplementation may be an effective, and most importantly, an easy to adhere conservative treatment that could significantly improve the quality of life of adults with obesity and concurrent metabolic knee OA. If proven to be successful, prebiotic supplementation could impact the health care system with reduced costs and potentially improved outcomes by targeting not only metabolic outcomes as previously shown with prebiotics [20–27], but also functional outcomes associated with less pain and improved knee function. Additionally, if effective, a regimen of prebiotic supplementation could provide a window of opportunity to motivate patients and improve their quality of life, whereby a reduction in knee joint pain through changes in gut microbiota could allow individuals to increase their physical activity or subsequently engage in an exercise program specifically aimed at restoring knee joint function due to OA. Lastly, positive findings from the present study could have the potential to postpone or potentially prevent the need for more aggressive treatment modalities for adults with obesity and concurrent knee OA, such as knee joint replacement.

This double-blind, placebo-controlled clinical trial is not without limitations and steps have been taken to reduce potential confounders and bias. First, this is an extensive and long-term study (9 months in total) and we speculate that participants may withdraw from the study. In order to accommodate for such losses, we will enroll 30% more participants than required on our sample size calculations. In some patients, oligofructose and inulin can cause result in increased flatulence and bloating. To minimize abdominal discomfort, participants will be instructed to start on a lower dose for the first 2 weeks to allow the digestive system to adjust to the increased intake of fermentable substrate. Finally, given the long duration of the study, patients might undergo lifestyles changes from the time of baseline assessments. To be able to monitor potential changes, dietary intake will be recorded with 3-day food records and physical activity monitored with self-report questionnaire and accelerometer results at 3 month intervals.

The work proposed here has the potential to identify a novel therapy that could alleviate some of the pressure on the growing demand for aggressive OA treatments such as total knee joint replacement at younger ages. Less aggressive, yet effective, conservative treatment options have the potential to address the growing prevalence of co-morbid obesity and knee OA by delaying the need for joint replacement or ideally preventing its need altogether. The results of this clinical trial will provide the first evidence regarding the effects of prebiotic supplementation on knee joint function and pain in adults with obesity who are also suffering from knee OA. If successful, the results may provide a simple, safe, effective, inexpensive, and easy to adhere intervention to reduce knee joint pain and improve the quality of life of adults with co-morbid knee OA and obesity.

## Trial status

The protocol (version 1.0, April 3, 2018) was approved by the Conjoint Health Research Ethics Board (REB17-2363), University of Calgary (Calgary, Alberta, Canada), on May 24, 2018, and was registered at ClinicalTrials.gov on 21 November 2019 (NCT04172688). Recruitment began in September 2018 and is expected to be completed by December 2021.

## Data Availability

Data is available for up to 5 years from the date of publication upon reasonable request.

## Abbreviations

OA: Osteoarthritis
SCFA: Short-chain fatty acids
HFS: High-fat/high-sucrose
BMI: Body mass index
DXA: Dual energy x-ray absorptiometry
OARSI: Osteoarthritis Research Society International
NPRS: Numerical pain rating scale
KOOS: Knee injury and osteoarthritis outcomes score
METs: Metabolic equivalent
NMR: Nuclear magnetic resonance
ANOVA: Analysis of variance
FDR: False discovery rate
NMDS: Non-metric multidimensional scaling
